**Fig. 2 Fig2:**
[figure not shown]
Study clusters in five arms with close-up view of one union for illustration

### Sample size

Each study cluster comprised of an average population of 2000 and necessary adjustments were considered for cluster randomization. Crude birth rate (CBR) in rural Bangladesh in 2011 was 23 live births per 1000 population [25]. Therefore, taking six months of recruitment window for pregnant women, each cluster would have yielded ~23 new pregnancies on average.

Several assumptions were considered for the sample size calculation [26]. The first assumption was that mean LAZ (our primary outcome variable) for 18–23 months old children in the comparison arm will be −2.0, and standard deviation of mean LAZ in both intervention and comparison arms will be 1, based on the mean HAZ reported in this age group in the BDHS 2011. These BDHS 2011 [25] parameters were the latest available during this protocol development. The estimates were still valid in 2015 since the latest BDHS (2014) showed similar stunting rates in *Sylhet* division [11]. Second, a 0.4 difference in mean LAZ score was expected in intervention arms compared to comparison. As the third assumption, we considered an 80% power and 5% alpha; the inter-cluster correlation coefficient of 0.06, derived from the design effect for HAZ in BDHS 2011, was used for adjustment of clustering effects. Fourth, the ratio between 4 intervention and 1 comparison arms was set at 1:1:1:1:1. Taking all the above assumptions into account, the Stata SE 13 software calculated the sample size to be 175 children per arm, which can be yielded from 25 clusters. However, to examine the secondary outcome variables between the comparison arm and individual intervention arm with a higher statistical power, the sample size in the comparison arm was doubled, thus the ratio between participant numbers in each intervention arm and comparison arm was raised to 1:2, respectively. The final allocation ratio of study participants was thus 1:1:1:1:2 for intervention arm 1: intervention arm 2: intervention arm 3: intervention arm 4: comparison arm 5. Thus, the final sample size was 175 children in each intervention arm and 350 children in the comparison arm. Considering the characteristics of the intervention, however, enrolment was during pregnancy. We therefore considered the following losses- 11% pregnancy loss due to abortion and still births (personal communication from Health and Demographic Surveillance System run by icddr,b at Mirzapur, Tangail), a 4% mortality in the first two years of life [25], 15% losses due to non-consent to participate by eligible women and loss-to-follow up. Loss-to-follow up includes refusal and migration out of study area. Thus, final sample size considering participant recruitment during pregnancy was 250 pregnant women in each intervention arm and 500 pregnant women in the comparison arm which is expected to yield the required number of children at 24 months from the enrolled cohort.

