**Methods:**

This community-based cluster randomised trial (c-RCT) compares 4 intervention combinations against one comparison arm. Intervention combinations are: 1) Behaviour change communication (BCC) on maternal nutrition during pregnancy, exclusive breastfeeding, and complementary feeding, along with prenatal nutritional supplement (PNS) and complementary food supplement (CFS); 2) BCC with PNS; 3) BCC with CFS; and 4) BCC alone. The comparison arm receives only routine health and nutrition services. From a rural district, 125 clusters were selected and randomly assigned to any one of the five study arms by block randomisation. A bespoke automated tab-based system was developed linking data collection, intervention delivery and project supervision. Total sample size is 1500 pregnant women, with minimum 1050 resultant children expected to be retained, powered to detect a difference of at least 0.4 in the mean LAZ score of children at 24 months, the main outcome variable, between the comparison arm and each intervention arm. Length and other anthropometric measurements, nutritional intake and other relevant data on mother and children are being collected during enrolment, twice during pregnancy, postpartum monthly till 6 months, and every third month thereafter till 24 months.

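### The stated 175 children per arm at 80% power does not follow from the printed inputs with 25 clusters per arm; the discrepancy is conservative, but an input, the size or the power is misreported.

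*Protocol article*

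**What the plan says.** The Sample size section sets out the calculation in full. The effect is "a 0.4 difference in mean LAZ score was expected in intervention arms compared to comparison". The spread is given as "standard deviation of mean LAZ in both intervention and comparison arms will be 1", which can only sensibly mean the SD of individual LAZ values. For error rates, "we considered an 80% power and 5% alpha"; sidedness is not stated. Clustering is handled with "the inter-cluster correlation coefficient of 0.06, derived from the design effect for HAZ in BDHS 2011". For allocation, "the ratio between 4 intervention and 1 comparison arms was set at 1:1:1:1:1". From these the software "calculated the sample size to be 175 children per arm, which can be yielded from 25 clusters".

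The comparison arm was then doubled to raise power for secondary outcomes, so "the final sample size was 175 children in each intervention arm and 350 children in the comparison arm".

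The layout is fixed elsewhere in the article. The section on cluster randomization and intervention allocation describes 125 clusters randomised in 25 blocks of five, hence 25 clusters in every arm. Participant recruitment gives 10 women per intervention cluster and 20 per comparison cluster. With the 30% total losses assumed (11% + 4% + 15%), these become 7 and 14 children per cluster at 24 months.

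The article does not say which cluster size was entered into the software.

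**The concern.** Every input needed to repeat the calculation is printed, together with the result and the number of clusters, yet the result cannot be reached from the inputs in that layout. This differs from a detail that a condensed article leaves to a fuller document: it is a published calculation that does not agree with its own figures.

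What is at stake is knowing which number is wrong. If the correlation really used was near 0.13, then 175 and 80% are both right and the printed 0.06 is wrong. If the printed inputs are right, the 80% understates the power of the primary comparison, and the doubled comparison arm raises it further. A reader cannot tell these cases apart, and anyone reusing the calculation for a similar trial would carry the error forward.

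**Working it through.** **Inputs** (Sample size section unless noted): difference 0.4; SD 1; power 80%; alpha 5%, taken as two-sided; ICC 0.06; 1:1 per pairwise comparison; 25 clusters per arm (also from 125 clusters over five arms). Equal cluster sizes are assumed throughout.

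**1. Unclustered size per arm**

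n₀ = 2 × (1.96 + 0.8416)² / 0.4² = 98.1

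**2. Trying to reproduce 175**

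Design effect DE = 1 + (m − 1) × 0.06, with m children per cluster.

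- In the design's own layout m = 175/25 = 7, so DE = 1.36 and n = 98.1 × 1.36 = 133.4. That is 134 children in about 19 clusters (133.4/7 = 19.1).
- With the number of clusters fixed at k = 25 per arm, m = n₀(1 − ICC)/(k − n₀ × ICC) = 98.1 × 0.94/(25 − 5.89) = 4.83, so about 121 children, or 125 at a whole 5 per cluster.

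The stated 175 is 31% above 134 (175/134 = 1.31) and 40 to 45% above 121–125. Rounding does not explain this.

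These sizes rest on the normal approximation. With t on 48 df, 125 children in 25 clusters give 79% power rather than 81%; 134 children at 7 per cluster give about 78%. The t correction adds a few children and does not close the gap to 175.

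**3. Which changed inputs give about 175**

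| Change | Result per arm |
|---|---|
| 14 per cluster (DE 1.78) | 98.1 × 1.78 = 174.6, i.e. 12.5 clusters per arm |
| 90% power, 7 per cluster | 131.3 × 1.36 = 178.6 |
| 85% power, 10 per cluster | 112.2 × 1.54 = 172.8 |
| ICC 0.13, 7 per cluster | (175/98.1 − 1)/6 = 0.131 solves for 175 |
| One-sided 5%, 7 per cluster | 77.3 × 1.36 = 105.1 (no match) |
| Alpha 0.0125, 7 per cluster | 139.4 × 1.36 = 189.6 (no match) |

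The closest match, 14 per cluster, would arise if 25 had been entered as the total for two arms. That is an inference; the article does not say so.

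**4. Power of the stated sizes if the printed inputs stand**

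SE² = DE₁/n₁ + DE₂/n₂; power = Φ(0.4/SE − 1.96), checked with a noncentral t on 48 df; detectable difference at 80% power = 2.802 × SE (normal) or 2.860 × SE (t).

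| Comparison, 25 clusters per arm | SE | Power, normal | Power, t | Detectable difference |
|---|---|---|---|---|
| 175 v 175 (7 and 7 per cluster) | √(2 × 1.36/175) = 0.1247 | 89.4% | 88.2% | 0.35 (t: 0.36) |
| 175 v 350 (7 and 14 per cluster) | √(1.36/175 + 1.78/350) = 0.1134 | 94.2% | 93.3% | 0.32 (t: 0.32) |

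If cluster sizes varied with a coefficient of variation of 0.5 (an assumption), the normal-approximation powers would be 87% and 92%.

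**The case against.** The best defence is that the cluster size entered is never stated. The figure of 7 comes from dividing 175 by 25, and the mention of 25 clusters can be read as a remark on feasibility made after the calculation. On that reading the software may have been correct for what it was given, since 14 per cluster returns 174.6. This stands to the extent that one cannot say which figure is at fault, and 14 per cluster is not the only route to about 175. It does not rescue the passage: 14 per cluster under equal allocation contradicts 25 clusters per arm, and the other routes contradict the printed power or ICC.

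It is also fair to say that the discrepancy is conservative, that a null result would be read from its estimate and confidence interval rather than from the planned power, and that nothing in the conduct of the trial depends on the correction. All of this stands and limits the weight of the point.

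Three stronger readings are tempting and are not supported. A reader might infer that the trial is underpowered; on the printed inputs it has more power than claimed. A reader might infer that the abstract is wrong where it calls the trial "powered to detect a difference of at least 0.4 in the mean LAZ score"; it gives no percentage, it is true at 93–94% power, and 0.4 is presented in the article as the expected effect, not as the smallest detectable one. A reader might also want power figures adjusted for four comparisons, for example by Dunnett's method; the article specifies no such procedure, so those figures do not belong to this correction.

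**Conclusion.** The point holds. The printed inputs and the printed layout require about 134 children per arm at 7 per cluster, or about 121–125 with 25 clusters fixed, not 175. Either one of the inputs is misreported or the stated 80% power is wrong, and only the sponsor can say which. If the inputs are right, the stated sizes give roughly 9 percentage points more power than claimed under equal allocation and about 14 points more in the final layout. The conclusion rests on a two-sided 5% test and equal cluster sizes; neither a one-sided test nor the t correction brings the figure to 175. Because the error runs in the safe direction under the printed inputs, this is a reporting correction that should be made, not a threat to the primary comparison.

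**What to change.** In the Sample size section, state the number of children per cluster and clusters per arm that were entered, and whether alpha was two-sided. Then correct the figure that is wrong:

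- If a different ICC, power or cluster layout was used, print that value and reconcile it with 25 clusters per arm.
- If the printed inputs stand, keep 175 and 350 as the chosen sizes but replace the 80% with the power they give for a difference of 0.4: about 88–89% for 175 v 175 and 93–94% for 175 v 350 in 25 clusters per arm. Give the difference detectable at 80% power as about 0.35–0.36 and 0.32, and say that equal cluster sizes are assumed. If 134 or 121–125 is quoted as the size for 80% power, label it a normal approximation.

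The abstract can stay as it is. The cost is a few sentences of text, with no change to enrolment, clusters or data collection.

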
### Participant recruitment

We enrolled 10 pregnant women in each intervention cluster and 20 in each comparison cluster, following the inclusion and exclusion criteria for participant eligibility (Table 1). Data collectors systematically conducted door-to-door surveys of all households in the study area to identify newly pregnant women, which were repeated in subsequent monthly cycles. The woman’s pregnancy status was assessed by enquiring about the first date of her last menstrual period (LMP), and possible pregnancy was confirmed with a sensitive pregnancy urine test kit (Excel®). Women tested positive were invited to voluntarily participate in the study with appropriate informed written consent. Recruitment of eligible pregnant women started in November 2015 and was completed in May 2016. Follow up of the cohort is ongoing.

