### Cluster randomization and intervention allocation

We purposively selected two adjacent sub-districts (*Bahubal* and *Nabiganj*) of *Habiganj* district. These two sub-districts have a total of 20 unions (lowest administrative unit). We excluded 8 unions, 3 being in hard-to-reach areas (seasonal flooding and poor road transport system) and 5 having intensive nutrition intervention projects implemented by other non-government organisations (NGOs). The remaining 12 unions had enough population to cover the desired sample size. Each union was then divided into clusters, each cluster comprising of ~450 households or ~2000 population (average 2–3 villages). We selected five clusters or multiples of 5 clusters from each union, 125 clusters in total following the cluster exclusion criteria detailed in Table 1. We then applied block randomisation by generating random sequence of 1–5 (each number representing a specific study arm) of 25 blocks with the analytical software Stata SE 14.2. Clusters were then allocated to arms, five at a time, based on the random sequence (Fig. 2). Taking equal numbers of clusters per arm from each union will ensure neutralizing the effect of variations, if any, of background characteristics between the unions. Allocation concealment was impractical due to community-based study design and nature of BCC intervention. However, care is taken to keep the outcome assessors blinded to the interventions allocated to specific clusters. The intervention and the evaluation teams have minimal contact to minimise information bias.

**Table 1 Tab1:** Inclusion and exclusion criteria

Exclusion criteria for clusters	
• Similar nutrition interventions currently being implemented by either government or non-government agencies in the selected cluster • The cluster is too hard to reach • The cluster includes tea gardens. Communities in tea gardens comprise of unique ethnicity, culture and lifestyle for which our intervention is not customized.	
Inclusion criteria for participants	
• All newly identified pregnant women aged 15 to 49 years • Gestational age ≤ 125 days • Permanent residents of the study area.	
Exclusion criteria for participants	
• Woman could not recall last menstrual period (LMP). • Woman not a permanent resident of the study area

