### Data collection

All questionnaire-based data and anthropometric measurements are collected by trained data collectors. Anthropometric measurements are taken following measurement-specific standard operating procedure [38]. Measuring tools are calibrated regularly. All data collectors are female and locally recruited. Before initiation of participant recruitment, the data collection team was intensely trained by the central team on all aspects of data collection, including consent taking, different data collection methods, anthropometric measurements, question throwing techniques, use of the tablet and cultural aspects to consider during data collection. Monthly meetings are held for troubleshooting and refresher trainings are conducted as needed. Following the initial training, all data collectors were standardised for anthropometric measurements against two gold standard trainers from icddr,b. Subsequently, refreshers trainings are conducted every two months to retain measurement standards. The data collectors are directly supervised by two FRAs who monitor data collection quality and provide on-site feedback as needed. One field manager is responsible for overall field coordination.

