### Process evaluation

#### Adherence to supplements for both mothers and children

Empty supplement sachets are collected and supplement tracking is carried out in each visit by the CHWs. Besides, we are assessing supplement compliance using a structured questionnaire with some open questions with queries on respondents’ attitude and practice towards the antenatal and complementary food supplements provided to them. We would collect similar data for checking compliance of complementary supplements to children aged 6 months to 24 months (in associated arms).

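### The 10-versus-20 enrolment quota probably puts comparison-arm births about a month later, and the stated models carry no term for birth month

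*Protocol article*

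**What the plan says.** Under Sample size, all clusters are described alike: "Each study cluster comprised of an average population of 2000", and "Crude birth rate (CBR) in rural Bangladesh in 2011 was 23 live births per 1000 population". From these the article concludes that over a six-month window "each cluster would have yielded ~23 new pregnancies on average". The same section doubles the comparison arm, giving 250 women in each intervention arm and 500 in the comparison arm.

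Participant recruitment achieves this by quota: "We enrolled 10 pregnant women in each intervention cluster and 20 in each comparison cluster". Data collectors went door to door in repeated monthly cycles, and women who tested positive were invited to join. "Recruitment of eligible pregnant women started in November 2015 and was completed in May 2016". Table 1 admits newly identified pregnancies up to 125 days' gestation. The article gives no rule for choosing the 10 or 20 women and does not say that a cluster closed when its quota was reached.

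The Statistical analysis plan section names household food security, education and socio-economic status as possible confounders, to be controlled if randomisation leaves them unbalanced. It names neither enrolment date, birth month nor season.

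On blinding, Cluster randomization and intervention allocation says that allocation concealment was impractical but that "care is taken to keep the outcome assessors blinded to the interventions allocated to specific clusters". Data collection says "All questionnaire-based data and anthropometric measurements are collected by trained data collectors". The section on adherence to supplements adds that "we are assessing supplement compliance using a structured questionnaire with some open questions".

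**The concern.** Each arm has 25 clusters of similar size, so doubling the comparison arm means taking twice as many women from clusters that produce pregnancies at the same rate. Filling 20 places from the same stream takes longer than filling 10. If places were filled in order of detection, the comparison arm runs later in the calendar because of the enrolment rule, not by chance, and randomising the clusters does not remove that.

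LAZ standardises for age and sex, not for the season of conception or birth. Study setting describes an area with 77% household food insecurity, so a seasonal influence is plausible. If there is one, it shifts the shared comparator and so moves all four primary contrasts in the same direction. Contrasts among the four intervention arms are not affected, because those arms share one quota.

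A second consequence concerns blinding. The staff group that enrols up to 10 women in some clusters and 20 in others is also the group that measures length. The number enrolled can show which clusters are comparison clusters.

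**Working it through.** **1. The article's own figures.**
- Yield per cluster: 2000 × 23/1000 × 0.5 year = 23, as stated.
- Quotas: 25 × 10 = 250 and 25 × 20 = 500, as stated.

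**2. Time to fill, if women are enrolled as found at a constant rate.** The rate is 23/6 = 3.83 a month.
- Quota of 10: 10/3.83 = 2.6 months.
- Quota of 20: 20/3.83 = 5.2 months.
- Difference in mean enrolment date: (5.2 − 2.6)/2 = 1.3 months.

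The article's own loss figures give a range. Raising the rate for 11% pregnancy loss (23/0.89/6 = 4.31 a month) gives 2.3 v 4.6 months and a shift of 1.2. Cutting it for 15% losses (3.83 × 0.85 = 3.26) gives 3.1 v 6.1 months and a shift of 1.5.

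**3. Allowing for existing pregnancies.** With entry allowed up to 125 days' gestation, the first round also finds women already pregnant. A simulation of seven monthly cycles at the same three rates, assuming detection from day 35, puts the comparison arm later by 17 to 31 days in mean enrolment date and by 27 to 43 days in mean last menstrual period. Birth dates should follow the latter. Across both approaches the shift is roughly 0.6 to 1.5 months.

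**4. Overlap.** In simulations with 2.5 to 3.83 pregnancies a month, with and without existing pregnancies, the month distributions of last menstrual period overlap by about 64% to 75% between arms. About 8% to 22% of comparison women lie beyond the 99th percentile of the intervention arms' dates.

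**5. Possible bias in LAZ.** The documents give no seasonal amplitude, so this step is an assumption. Take a yearly cosine with half-amplitude A. Its mean over a window of w months has modulus S(w) = sin(πw/12)/(πw/12) and phase πw/12.
- For w = 2.6: S = 0.924, phase 0.683.
- For w = 5.2: S = 0.717, phase 1.366.
- Largest difference: √(0.924² + 0.717² − 2 × 0.924 × 0.717 × cos 0.683) = 0.58, times A.
- Mean absolute difference over all phases: 0.58 × 2/π = 0.37, times A.

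| Assumed peak-to-trough swing | A | Worst phase | Average over phase |
|---|---|---|---|
| 0 | 0 | 0 | 0 |
| 0.2 | 0.1 | 0.06 | 0.04 |
| 0.4 | 0.2 | 0.12 | 0.07 |

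The worst-phase values are about 15% and 29% of the 0.4 target. A cruder calculation that shifts the whole distribution by 22 to 40 days, 2A sin(πd/365), gives 0.04 to 0.07 for A = 0.1 and 0.08 to 0.14 for A = 0.2, which is the same order.

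**6. Scale against sampling error.** With SD 1, ICC 0.06, and 7 and 14 children per cluster (175/25 and 350/25), the design effects are 1.36 and 1.78. The standard error is √(1.36/175 + 1.78/350) = 0.113. The worst-phase bias is therefore 0.5 to 1.0 standard errors.

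**7. Blinding.** Set side by side, the sections say that data collectors find and enrol women, that data collectors take all anthropometry and questionnaire data, and that outcome assessors are kept unaware of allocation. The first two make the third hard to sustain for comparison versus intervention clusters. The quota does not separate the four intervention arms from each other.

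**The case against.** The strongest objection is that consecutive filling is an inference. The article states no selection rule, and a condensed article may omit one without fault. If the 10 women were spread over the whole window, there is no date shift. This stands, and the conclusion is conditional on it. The text does lean the other way: it admits newly identified pregnancies, invites women who test positive and describes no sampling step. Spreading would also leave an arm-dependent selection, 10/23 = 43% v 20/23 = 87% of expected pregnancies, by staff working without allocation concealment.

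A reader might infer that the later half of the comparison women has no same-season counterpart in the intervention arms. The documents do not support this. Monthly cycles, variable accrual and existing pregnancies produce the partial overlap in step 4.

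A reader might also take 0.06 to 0.12 LAZ as the expected bias. It is a worst-phase maximum on an assumed swing. By 24 months every child has lived through two full years, and the effect may be near zero.

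It is also tempting to say that no analysis corrects the problem. A separate analysis plan may add covariates. What can be said is that the article does name its covariates and birth month is not among them. No model could correct unblinding in any case.

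Finally, a reader might conclude that blinding is defeated. The article identifies a staff category. It does not say that the same individuals recruited and later measured in a cluster, or that they knew what the quota meant. Supplements in the home and compliance questions could reveal allocation regardless of the quota. Unblinding is likely but not documented.

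**Conclusion.** The concern holds in a conditional form. The quota is an arm-dependent enrolment rule applied after randomisation to clusters with equal expected yield. If women were enrolled as found, the comparison arm's mean conception and birth date is about one month later (roughly 0.6 to 1.5), with partial overlap of months. The stated models leave this imbalance in. Any seasonal effect on LAZ would then enter all four comparisons with the comparison arm, in a direction that cannot be predicted from the documents. Its size rests wholly on an assumption: at most about 0.06 to 0.12 LAZ for a swing of 0.2 to 0.4, about 0.04 to 0.07 averaged over phase, and near zero if season does not matter.

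This does not show that the results will be biased. It shows a probable structural imbalance that data already being collected can remove cheaply. The blinding point is secondary: the sections on recruitment, data collection and blinding need to be reconciled.

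**What to change.** **Analysis.**
- Include calendar month of birth, as month indicators or sine and cosine terms, in every comparison with the comparison arm, regardless of baseline balance.
- State how the 10 or 20 women were chosen, and report enrolment month and birth month by arm.
- Add a sensitivity analysis limited to the first 10 women enrolled in each cluster, which gives every arm the same quota.

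**Measurement.**
- Reconcile the blinding statement with data collectors enrolling to an arm-specific quota.
- Where this is not already practice, record and lock length in the tablet before feeding or supplement questions open, and assign the 24-month length to an existing collector other than the cluster's recruiter.

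**Cost.** The changes need analysis wording, possibly a change in form order and a rota among existing staff; no new data are required. The first-10 analysis halves the comparison sample and is less precise. There was still time for this when the article appeared in May 2017: a woman enrolled in November 2015 at 125 days' gestation would, assuming a 280-day pregnancy, give birth about 155 days later, around April 2016, so 24-month visits start around April 2018.
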